## Methods

### Partners

The CARDIOCARE prospective study is multicentric and involves 6 European clinical partners: the IEO—the study clinical coordinator—in Italy, the BOCOC in Cyprus, the KSBC in Sweden, the UOI and NKUA in Greece, and the Institute of Oncology Ljubljana (IOL) in Slovenia. The work of these clinical centers, and especially the technological aspects of eHealth tool implementation, is supported by 5 European technical partners: the Foundation for Research and Technology, the Hellenic Mediterranean University, and the UOI, all based in Greece; Stremble, a research and development company based in Cyprus offering a range of advanced analytics, bioinformatics, and software engineering expertise; the European Society of Cardiology based in France; and the Philips Electronics Nederland B.V. company in the Netherlands. The Institute of Health Management in Italy is also part of the CARDIOCARE consortium, ensuring the highest level of study conduct and management quality.

### Study Design

This multicenter clinical study has been designed as a prospective observational study that examines whether integrated patient-oriented psychological, behavioral, and functional interventions can prevent, delay, or mitigate cardiotoxicity as an adverse effect of cancer therapy. It will include 750 older patients with breast cancer recruited across the participating clinical centers.

All recruited patients will be randomly assigned to either the standard practice or enhanced monitoring group. Patients in both arms, in addition to standard oncological care, will receive eHealth monitoring through the Garmin Venu SQ and Polar H10 technologically advanced wearable devices (described in detail in the Instruments and Measures section) and will have access to the ePsycHeart assessment tool on the CARDIOCARE mobile app (described in detail in the Instruments and Measures section). Furthermore, patients will be given a Motorola smartphone on which the CARDIOCARE mobile app is installed. These technological instruments will provide clinicians with the patients’ physical and psychological intrinsic capacity and QoL indicators as foreseen in the study protocol. However, only patients in the intervention arm will have access to the behavioral, psychological, functional, and educational interventions in the eHealtHeart section of the CARDIOCARE mobile app, which will allow researchers to evaluate the effectiveness of such eHealth interventions on the intrinsic capacity and QoL of older patients with breast cancer, as well as these interventions’ effectiveness in mitigating, delaying, or even preventing the onset of cardiac toxicity associated with breast cancer treatments.

As per the protocol, before undertaking any study procedure, the patients will receive a patient information sheet, in which the different study procedures are explained in lay language. The same document also sets out the study’s risks, benefits, and aims. Once the patient has read the patient information sheet and has received answers to any questions or concerns, she can choose to provide informed consent to participate in the study by signing the written informed consent form, of which she will be left with a copy, whereas the CARDIOCARE researchers will keep the original document.

Patients will be assigned through the study electronic case report form (eCRF) at baseline to the standard practice or enhanced monitoring group in a 1:1 ratio. The study time points, follow-ups, and specific procedures are detailed in the Study Time Points and Procedures section (Figure 1).

**Figure 1 figure1:**
[figure not shown]
Study design. BNP: brain natriuretic peptide; FU: follow-up; PREM: patient-reported experience measure; PROM: patient-reported outcome measure; QoL: quality of life; SNP: single-nucleotide polymorphism.

Great attention has been paid to the standardization of procedures among the clinical centers involved. Specifically, the inclusion criteria for the study are thoroughly detailed and are consistent across all 6 clinical centers involved in recruitment. This ensures that the same standards are followed at each site, allowing for a homogeneous participant selection process.

In addition, the technical partners involved in the study are responsible for continuously monitoring the data entered into the eCRF. They actively identify any values that may require further scrutiny or validation, ensuring the quality and integrity of the data.

Furthermore, the CARDIOCARE platform plays a crucial role in the standardization process. It provides real-time monitoring of whether patients are adhering to the prescribed activities according to the study protocol. If any discrepancies are detected, the clinical centers can contact their patients to address any issues, ensuring that all sites are aligned with the study protocol.

Therefore, while working across multiple centers presents certain challenges, the combination of detailed inclusion criteria, constant monitoring through eCRFs, and checks via the CARDIOCARE platform makes the process both feasible and practical. This multilayered approach allows for high levels of standardization and consistency across all sites.

Potential sources of bias have been minimized as follows. Regarding recall bias, the same questions are asked in both groups, ensuring that the bias is homogeneous, and reminders are sent to patients to complete the questionnaire on time. Regarding selection bias, the inclusion criteria are stringent, and all suitable candidates are enrolled by the centers. Regarding confirmation bias, the primary end points and most secondary end points are quantitative, reducing the likelihood of interpretation errors. Regarding observation bias, some questions are repeated across questionnaires, and patients complete the same questionnaire 3 to 5 times during the study.

### Study Participants

A total of 750 women aged ≥60 years with a diagnosis of breast cancer will be recruited across the 6 European clinical centers involved in the CARDIOCARE consortium in Italy, Greece, Cyprus, Sweden, and Slovenia (IEO: n=125, 16.7%; BOCOC: n=120, 16%; KSBC: n=125, 16.7%; UOI: n=60, 8%; NKUA: n=195, 26%; IOL: n=125, 16.7%). A subsample of 500 patients will be randomly selected (IEO: n=100, 20%; BOCOC: n=100, 20%; KSBC: n=80, 16%; NKUA: n=130, 26%; IOL: n=90, 18%) to allow Stremble to assess gut microbiome changes associated with oncological treatments. Details on the inclusion and exclusion criteria to recruit patients are provided in the Selection Criteria section.

### Selection Criteria

#### Inclusion Criteria

The inclusion criteria are as follows: (1) women aged ≥60 years with a diagnosis of early or locoregional breast cancer who will undergo neoadjuvant or adjuvant treatment with regimens including anthracyclines or taxanes; (2) women aged ≥60 years with a diagnosis of human epidermal growth factor receptor 2 (HER2)–positive early or locoregional breast cancer who will undergo neoadjuvant or adjuvant treatment with anti-HER2 therapy (trastuzumab or trastuzumab and pertuzumab); (3) women aged ≥60 years with a diagnosis of early or locoregional breast cancer who will undergo neoadjuvant or adjuvant treatment with endocrine therapies with or without cyclin-dependent kinase 4 or 6 inhibitors; (4) women aged ≥60 years with HER2-positive metastatic breast cancer who will undergo first-line anti-HER2 therapy (trastuzumab or trastuzumab and pertuzumab with or without chemotherapy); (5) women aged ≥60 years before starting the aforementioned treatment for breast cancer; (6) eligible women aged ≥60 years who will undergo first-line therapy in the metastatic setting with any type of treatment (chemotherapy, immunotherapy, or biological agents); (7) willingness and ability to comply with scheduled visits, laboratory tests, and other trial procedures; (8) ability to understand the provided information and provide written informed consent; (9) affiliation to a social security system; and (10) life expectancy of at least 12 months.

#### Exclusion Criteria

The exclusion criteria are age of <60 years and a diagnosis of severe psychiatric or neurological disorders that might impair the ability to provide informed consent.

### Study Time Points and Procedures

After the patient has signed the written informed consent form, she will follow the study procedures set for each time point, as shown in Table 2. Table 3 shows all self-administered scales that the patient has to complete for each study time point. These procedures are the same for both the standard practice and enhanced monitoring groups.

**Table 2 table2:** Summary of scheduled procedures.

Procedure	Day −15: T0 (screening)^a^	T1 (baseline)^a^	Day 0: treatment start	Month 3: T2	Month 6: T3	Month 9: T4	Month 12: T5	14-25 days after the end of treatment^b^
ICF^c^ signature	✓							
Diagnosis	✓							
Personal and family medical history (including diagnosis of severe psychiatric disorders)	✓							
Smoking habits		✓						✓
Comorbidities	✓							
Oncological visit		✓			✓		✓	
Psychological visit^d^ (if the center has a psychological support service)		✓		✓	✓	✓^e^	✓	
Cardiological visit (if needed)	✓	✓		✓	✓	✓^e^	✓	
BP^f^ and HR^g^ measurement		✓		✓	✓	✓^e^	✓	
Routine blood analysis (ie, hematology and biochemistry)^h^		✓		✓	✓	✓	✓	
Echocardiographic assessment^i^		✓		✓	✓	✓^e^	✓	
ECG^j^ assessment		✓		✓	✓	✓^e^	✓	
Plasma troponin I level assessment	✓^k^	✓^k^		✓	✓	✓	✓	
Mammography (if the patient did not undergo mastectomy)		✓					✓	
Plasma BNP^l^ assessment		✓		✓	✓	✓	✓	
Plasma myeloperoxidase and high-sensitivity CRP^m^ assessment (if available)		✓		✓	✓	✓	✓	
Inclusion and exclusion criteria checklist	✓							
Blood sample for genetic analysis		✓						
Plasma sample for micro-RNA analysis		✓						✓
Stool sample		✓						✓
Oncological treatment (plan and changes) and cycle			✓	✓	✓	✓	✓	✓
Information on treatment status (ongoing or completed)				✓	✓	✓	✓	
Concomitant medications	✓	✓	✓	✓	✓	✓^e^	✓	✓
GSRS^n^		✓						✓
Patient lifestyle questionnaire		✓						✓
Verification of completion of self-administered scales and questionnaires (ePsycHeart section)^o^		✓	✓	✓	✓	✓	✓	
Cognitive effect assessment (if the center has specialized personnel)		✓			✓		✓	
Verification of collection of data from wearable devices				✓	✓			
Collection of information on patient’s out-of-pocket expenses					✓		✓	
Hand grip test		✓			✓		✓	
AE^p^ assessment		✓	✓	✓	✓	✓	✓	✓

^a^May be 1 or 2 visits.

^b^At the first visit after the end of each treatment, which should be within 14 to 25 days. The time of these sample collections will vary in relation to the therapeutic schedule of the patient.

^c^ICF: informed consent form.

^d^These visits can be conducted in person or remotely if the center can involve the required experts. The psychological visit consists of meeting the patient in person (if already at the clinical center) or remotely to touch base about the study—how they feel about it and whether they would like something to be different or modified. During the visit, a motivational intervention will also be carried out to minimize dropouts as much as possible.

^e^Only if possible.

^f^BP: blood pressure.

^g^HR: heart rate.

^h^Including cholesterols, glucose levels, and renal and liver function tests and interleukin-6, tumor necrosis factor, HR variability, C-reactive protein, fibrinogen, and ferritin if available.

^i^Including right and left ventricle dimensions and functions and diastolic function.

^j^ECG: electrocardiogram.

^k^Troponin can be analyzed either at screening or at baseline.

^l^BNP: brain natriuretic peptide.

^m^CRP: C-reactive protein.

^n^GSRS: Gastrointestinal Symptom Rating Scale.

^o^Table 3 provides a precise list of the questionnaires and scales administered at each time point.

^p^AE: adverse event.

**Table 3 table3:** Self-administered scales for each study time point.

Psychological or behavioral assessment	Day −15: T0^a^	T1 (baseline)^a^	Day 0: treatment start	Month 3: T2	Month 6: T3	Month 9: T4	Month 12: T5
Quality of life (EORTC^b^ QLQ-30^c^ and QLQ-BR23^d^)		✓		✓	✓	✓	✓
Fatigue (FACIT^e^-Fatigue)		✓		✓	✓	✓	✓
Resilience (Brief Resilience Scale)		✓		✓			✓
Anxiety and depression (PHQ-4^f^)		✓		✓	✓	✓	✓
Emotion regulation questionnaire (ERQ^g^)		✓		✓			✓
LOT-R^h^		✓		✓			✓
Life satisfaction (single-item life satisfaction measure)		✓	✓	✓	✓	✓	✓
Perceived social support (MSPSS^i^)		✓		✓			✓
Self-control and self-management (SCMS^j^)		✓		✓			✓
Coping strategies (CBI-B^k^)		✓		✓	✓	✓	✓
Post Traumatc Stress disorder (IES-R^l^)		✓		✓			✓
Perceived Stress (PSS^m^)		✓		✓	✓	✓	✓
Positive and negative affect (B-PANAS^n^)		✓		✓			✓
Burden for family caregivers (BSFC-s^o^)—optional		✓		✓	✓	✓	✓
Nutritional questionnaire		✓		✓			✓

^a^May be 1 or 2 visits.

^b^EORTC: European Organisation for Research and Treatment of Cancer.

^c^QLQ-30: Quality of Life Questionnaire.

^d^QLQ-BR23: Quality of Life Questionnaire–Breast Cancer.

^e^FACIT: Functional Assessment of Chronic Illness Therapy.

^f^PHQ-4: 4-item Patient Health Questionnaire.

^g^ERQ: Emotion Regulation Questionnaire.

^h^LOT-R: Life Orientation Test–Revised.

^i^MSPSS: Multidimensional Scale of Perceived Social Support.

^j^SCMS: Self-Control and Self-Management Scale.

^k^CBI-B: Cancer Behavior Inventory–Brief Version.

^l^IES-R: Impact of Event Scale–Revised.

^m^PSS: Perceived Stress Scale.

^n^B-PANAS: Brief Positive and Negative Affect Schedule,

^o^BSFC-s: short version of the Burden Scale for Family Caregivers.

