### Potential Limitations

This study’s psychological and behavioral monitoring is based on the use of a mobile app and wearable sensors, which may be problematic for some older adult users who are not familiar with or proficient in the use of this type of technology. Assistance and training in the use of the technology are provided at the recruitment stage, but the continued engagement with the app over the study period and compliance with the use requirements could pose significant obstacles to data collection. To circumvent this problem, the implementation of the study protocol includes frequent interaction between clinical staff and participants, as well as encouraging the involvement of family members to assist in maintaining compliance with the study protocols. This may result in a bias introduced by the level of technological dexterity of the patient, support in this regard from family members, or willingness to initiate communication with and seek help from clinical staff.

In addition, as with all multicenter studies, the study protocol is strictly applied and monitored at each clinical center to maintain consistency between centers. All equipment (eg, mobile phones and wearables) is the same and is provided through the CARDIOCARE project. Assessments of cardiotoxicity and subclinical cardiotoxicity are performed by a consensus group of cardiologists from each clinical center using all the available blood tests, echocardiograms, and treatment and patient history data. However, differences between populations, cultures, and environmental factors will be considered in the analysis plan to minimize any inherent bias.

Finally, a potential limitation of this project concerns the fact that the study follow-up period is limited to 12 months from the enrollment date to encompass both acute and early (within the first year) cardiotoxicity, defined based on imaging and biological biomarkers. Late cardiotoxicity (occurring up to several years after treatment) is not considered in this study.

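### The only follow-up stool sample is tied to the end of treatment with no fixed-time fallback, so women still on one continuous regimen at month 12 give no pair for the microbiome objective

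*Protocol article*

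**What the plan says.** Table 2 (Study Time Points and Procedures) ticks four linked items in two columns only, T1 and the end-of-treatment column: the stool sample, the row "Plasma sample for micro-RNA analysis", the GSRS and the patient lifestyle questionnaire. None is ticked at months 3, 6, 9 or 12.

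Footnote b defines the second column: "At the first visit after the end of each treatment, which should be within 14 to 25 days". It continues: "The time of these sample collections will vary in relation to the therapeutic schedule of the patient". The article states no latest date and no rule for treatment that has not ended.

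Study Participants selects 500 women at random "to allow Stremble to assess gut microbiome changes associated with oncological treatments".

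The Inclusion Criteria admit "neoadjuvant or adjuvant treatment with endocrine therapies with or without cyclin-dependent kinase 4 or 6 inhibitors" and women "who will undergo first-line therapy in the metastatic setting with any type of treatment". No duration is stated for either.

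Another row of Table 2 records at months 3, 6, 9 and 12 whether treatment continues or has finished. Under Potential Limitations, "the study follow-up period is limited to 12 months from the enrollment date".

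**The concern.** A collection point set by the end of treatment suits a finite course. It does not suit a regimen that may run past the end of follow-up, and the plan foresees such women because it asks about treatment status at month 12. For them the second stool sample never falls due.

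The stated purpose of the stool samples is to study change, which needs two samples from the same woman. The loss is not random: it follows the type of treatment. A class in which nobody finishes has no pairs, and no analysis method can recover them. In the metastatic setting, the women who do end first-line treatment within the year may be those who stopped early, for example for progression or toxicity. The pairs available there may then describe an unrepresentative group.

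**Working it through.** **Inputs from the article**
- Microbiome subsample: 500 (Study Participants).
- Planned dropout: 10% (Sample Size Considerations).
- Follow-up: 12 months (Potential Limitations).
- Collection times: T1, then 14 to 25 days after treatment ends (Table 2, footnote b).

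**Input not in the article**
- *f*, the share of the subsample with no end of treatment early enough to trigger a second sample by month 12. The article gives neither treatment durations nor the treatment mix, so *f* is an assumption and is shown as a range.

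**Step 1: the plan's own figure.** The centre allocations sum to 100 + 100 + 80 + 130 + 90 = 500, as stated.

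**Step 2: who gets a pair.** A second sample falls due within follow-up only if a treatment ends at least 14 days before month 12.

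| Treatment course | Second sample by month 12? |
|---|---|
| One finite course ending well before month 12 | Yes, after treatment |
| Sequential components, the last continuing past month 12 | Yes if *each* treatment means each component; no if it means the whole plan |
| One uninterrupted regimen continuing past month 12 | No, under either reading |

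The third row is the firm part of the point. Endocrine therapy alone and ongoing first-line metastatic therapy are the eligible examples.

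**Step 3: size as a function of *f*.** Pairs lost before dropout = 500 × *f*. Expected pairs after dropout = 500 × (1 − *f*) × 0.9, taking dropout as unrelated to treatment class.

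| Assumed *f* | Lost before dropout | Expected pairs after 10% dropout |
|---|---|---|
| 0 | 0 | 450 |
| 0.2 | 100 | 360 |
| 0.3 | 150 | 315 |
| 0.4 | 200 | 270 |
| 0.5 | 250 | 225 |

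**Step 4: within a class.** With *n* women in a class and a share *g* of them unfinished, expected pairs are *n* × (1 − *g*) × 0.9. If *g* = 1 this is 0, whatever the overall total.

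**Step 5: what a fallback would recover.** If every woman without an end-of-treatment sample gave one at month 12, the expected total would return to 500 × 0.9 = 450. At *f* = 0.5 that adds 450 − 225 = 225 pairs, all with an on-treatment or only just post-treatment second sample.

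**The case against.** **Condensed article.** The full protocol is not shown, and a rule for ongoing therapy might stand there. That would excuse silence on handling details. Here, however, the article prints the schedule itself, and that schedule followed exactly gives these women no second sample.

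**The word *each* in footnote b.** If it refers to components, women on sequential regimens give a sample when the first component ends. This stands, and it confines the certain loss to women on a single continuous regimen.

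**Legitimate design.** Sampling at a set distance from the end of treatment is a defensible, openly stated choice. That also stands. The problem is only the missing alternative when treatment has not ended.

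**Stronger readings that a reader might infer, and that the article does not support**
- *That the micro-RNA part of the risk model fails.* The article says that the model is enriched with omics markers and nowhere says that it needs before-and-after pairs. The baseline sample is usable in every treatment class. Nor does a tick in Table 2 prove that all 750 women give the sample, since stool is ticked too and is taken from a subsample.
- *That the aim of exploring each treatment separately fails.* In Novelty and Study Aim that sentence concerns quality of life and intrinsic capacity, which are measured at fixed visits.
- *That the randomized comparison is harmed.* Echocardiography, troponin I and natriuretic peptide have fixed visits.
- *That almost all endocrine-treated women are lost.* The criterion also covers neoadjuvant endocrine treatment, which is given before surgery and may end within the year. No durations are stated.

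**Conclusion.** The point holds for the microbiome objective. As written, the schedule yields no stool pair for a woman on one continuous regimen who is still on treatment at month 12, and the resulting gaps follow treatment class. That selection on early stopping affects the remaining metastatic pairs is plausible but not shown.

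The size is not known. The loss of 100 to 250 of 500 pairs before dropout rests entirely on an assumed 20% to 50% still on treatment. The GSRS and lifestyle questionnaire share the gap. So does the follow-up micro-RNA sample, but no stated analysis is shown to depend on its change.

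This is a worthwhile, inexpensive repair to a secondary part of the study. It is not a threat to the primary result.

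**What to change.** 1. Define in footnote b whether the end of each treatment means the end of a component or of the whole plan.
2. For any woman with no end-of-treatment sample by month 12, collect the second stool sample, micro-RNA plasma, GSRS and lifestyle questionnaire at the existing T5 visit.
3. Record treatment status (on or off) and days since baseline for every second sample.
4. Report on-treatment and post-treatment pairs separately.

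**Cost.** A short schedule amendment. T5 already includes an oncological visit and blood tests, so the additions there are a stool collection, an extra plasma sample and two questionnaires. A woman with no end-of-treatment sample gives one follow-up sample, which keeps her to the two already planned. Women already past month 12 when the change takes effect cannot be recovered this way. The change concerns research sampling only and alters no treatment.

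**Limit.** Some second samples will be taken on treatment. The fallback restores pairs within a class, but interval and treatment status will still track regimen, so differences between regimens should not be read as drug effects.

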### Instruments and Measures

All recruited patients will receive additional supportive care in conjunction with standard care. Patients in the standard practice group and those in the enhanced behavioral and psychological monitoring group of the study will receive wearable devices and complete an initial evaluation on the CARDIOCARE mobile app.

#### The CARDIOCARE Mobile App

The CARDIOCARE mobile app is installed on the Motorola smartphone provided to patients, which they will have to return after use (end of month 6—T3). The CARDIOCARE app allows access to 2 different settings containing specific modules (described in this section) depending on the group—standard practice or enhanced behavioral and psychological monitoring—the patient is assigned to.

The Cognitive Stimulation, Education and Training, Vision and Hearing, and Psychology and Well-being (except for the Questionnaires submodule) modules will only be accessed by the intervention arm of the study.

The six modules are (1) Mobility and Vitality, (2) Cognitive Stimulation, (3) Education and Training, (4) Geriatric Syndrome Assessment, (5) Vision and Hearing, and (6) Psychology and Well-being.

The Mobility and Vitality module contains 4 submodules, which are the nutrition questionnaire, physical activity, the cardio recording session, and the hand grip session. Together, these submodules will provide a collection of graphs—such as bar and pie charts—representing data on the patient’s overall functional well-being, sleep duration, physical activities, and average HR, as well as proxies of the patient’s stress levels.

The Cognitive Stimulation module includes 4 cognitive games, which are Find the Word, tic tac toe, Color Beans, and Drawing. If played consistently, such games can foster the patient’s attention, concentration, and working memory capacities, thereby counteracting the cognitive impairment often found in patients undergoing oncological treatments [21].

The Education and Training module includes 2 submodules. The first one is Breast Cancer Material, which contains patient-oriented information related to breast cancer and cardiotoxicity and on the potential psychological and social implications that breast cancer and its treatment can have. This submodule provides a deeper awareness about the clinical implications of the disease and guidance for the patients to preserve their psychological well-being. The second submodule is named Training and contains a video tutorial for patients to improve their balance and reinforce their muscle strength.

The Geriatric Syndrome Assessment module includes 2 submodules. The first one is Incontinence Management, which will allow each patient to report urination incidents, perform guided exercises for pelvic floor strengthening, and set reminders for toilet use. The second one is the Fall Mitigation submodule, where the patient can access the Otago program, a set of exercises designed to help them enhance and restore their balance [22].

The Vision and Hearing module includes the Vision Test and Hearing Test submodules. The first is an assessment of the patient’s vision capacity that was designed based on the Snellen test guidelines. The second one is an assessment of the patient’s hearing capability designed based on the whisper test guidelines.

Finally, the Psychology and Well-being module includes behavioral and psychological interventions corresponding to 5 submodules: expressive writing, BPS, ABCDE (A=activating event or situation; B=beliefs; C=consequences; D=disputation of beliefs; E=effective new approach), Biofeedback Session, and Questionnaires. The interventions in the first 4 modules aim to mitigate the psychological risk factors associated with cardiotoxicity development and deterioration of the patient’s QoL. The fifth submodule, Questionnaires, includes 15 self-reported measures that will provide critical information on the patient’s levels of perceived stress, resilience, anxiety and depression, self-management and emotion regulation capacity, coping skills, perceived social support, satisfaction with life, QoL, and levels of optimism (see Table 3 for the list of questionnaires used).

